**BIA**

To assess how health care budgets are changed by offering blended CBT for depression compared to CBT as usual, a *budget impact analysis* (BIA) will be conducted as outlined in Mauskopf et al. (2007). The BIA will include 1) the perspective of the public purse (in Dutch: Budgettair Kader Zorg), and 2) the perspective of the health care insurer and health care service provider. For each perspective, we consider costs when 10%, 20%, 30% and 100% of the target group receive bCBT. These scenarios will be compared with the base-case scenario, reflecting current care, where 0% of the target group is offered bCBT. When taking the societal perspective, we will consider the costs of offering the health care interventions (also the interventions offered in routine medical care for this particular target group), patients’ out of pocket costs, and costs stemming from productivity losses. Treatment costs will be based on the full economic cost prices (standard cost prices as reports in the Dutch Costing Manual). Productivity losses will be valued using the average gender and age specific productivity levels in the Dutch working population. When taking the perspectives of the public purse (BKZ) and the health insurance companies’ perspective, the focus will be restricted solely to the direct medical costs. For this, the average tariffs of the Dutch Health Authority will be used (NZa). The Budget Impact Analysis (BIA) will be conducted using a health economic (Markov cohort) simulation model.

## Secondary study parameter(s)

Outcomes on continuous clinical outcome variables, such as depressive symptoms, at T1, T2 and T3 (week 6-10, 12-20, and 64-72) are estimated for descriptive purposes through mixed-model analyses (MM), with participants as random effects, and time (T1-T3), group (blended vs. face-to-face treatment) and time x group as fixed effects, with baseline scores as a single covariate. To assess the magnitude of treatment effects, Cohen’s *d* effect sizes (Cohen, 1988) for each time point are calculated by dividing MM parameter estimates of fixed effects at each post-treatment assessment by the pooled standard deviation of outcome measurements at baseline (T0).

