## Sample size calculation

In economic evaluations we are calculating the power to estimate the joint distribution of costs and treatment effects. Subsequently, we need more information for estimating power compared to clinical trials, namely expected costs of treatments, expected covariance of treatment effects/costs, and the maximum willingness to pay for the treatment effect. To incorporate this information, the formula of Glick et al. (2011) can be used. A goal of sample size and power calculation for cost-effectiveness analysis is to identify the likelihood that an experiment will allow us to be confident that a therapy is acceptable or not when we adopt a particular willingness to pay.

For this study a sample size of 156 is based on a formula to estimate the power of a cost-effectiveness analyses. (Glick, 2011)

$$n=\frac{{2(z_{\alpha}+z_{\beta)}}^{2}\left( {sd}^{2}+\left( W^{2}{sd}^{2} \right)-\left( 2W\rho{sd}_{c}{sd}_{q} \right) \right)}{\left( WE-C \right)^{2}}$$

$$n=sample size/group$$

$$z_{\alpha}=z statistics for alpha$$

$$z_{\beta}=z statistics for Beta$$

$${sd}_{c}=Expected standard deviation costs$$

$${sd}_{e}=Expected standard deviation effects$$

$$W=Willingness to pay$$

$$C=Expected differences in costs$$

$$E=Expected differences in effects$$

$$\rho=correlation between differences in costs and effects$$

($z_{\alpha}=1,96$, $z_{\beta}=0,84$,${sd}_{c}=800$, ${sd}_{e}=0,02$, $W=80,000, C=832,E=0,02 \rho=0,1)$

Following the formula, we may expect that the point estimate for the cost-effectiveness ratio will be around 40,000 per quality- adjusted life year (QALY), using only a small increase in quality of life and lower costs for blended eHealth, we want to design an experiment that will provide an 80% chance (i.e., power) to be 95% confident that the therapy is good value when we are willing to pay at most 80,000 per QALY. In the Netherlands, a costs-effectiveness ratio between 20.000 and 80.000 Euro per QALY is assumed acceptable.

Glick, H.A. (2011). Sample size and power for cost-effectiveness analysis (part 1). Pharmacoeconomics, 29 (3), 189-198.

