**Blended CBT (bCBT)**

In the bCBT group, patients receive 6-10 face-to-face sessions and 6-10 internet sessions, which will be delivered over a period of 12-20 weeks. Treatment starts and ends with a face-to-face session. The online sessions are delivered through a secured web-based online treatment platform (Minddistrict; www.minddistrict.com). Patients access this platform with a personalized login. The website offers information that repeats and extends the contents of the face-to-face sessions. In addition, patients use the website to complete homework exercises, such as monitoring their activities, feelings, thoughts and behavior. The first online session focuses on working with the online platform. The therapist monitors patients’ online progress and provides weekly feedback prior to the next face-to-face session. Face-to-face sessions will be audio-recorded and checked, following the same procedures as in the CBT-TAU condition. Online sessions are recorded in the online treatment platform database. On completion of treatment, patients can still access the online treatment platform to re-read information and look up homework exercises, such as the relapse prevention plan.

The same medication regimes will be administered for both conditions throughout the study. Pharmacotherapy falls under the responsibility of a psychiatrist and is provided independently of the current study.

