**CEA/CUA**

Costs will be assessed at pre-, mid-, post-treatment and at one-year follow up. As the TIC-P cost date covers a period of three months, all costs will be extrapolated to a 12 months period assuming a stability of costs during the time frame. T-tests will test the change for each cost domain. As cost data will not be normally distributed, p-values will be estimated using a multilevel model (with repeated measurements to control for dependency between the measurements) after which a bootstrap analysis on the parameters is performed (10,000 replications, to generate a reliable cost estimate [23]. An incremental cost-effectiveness ratio (costs per case response or remission) and will be calculated (ICER =(mean costs blended eHealth treatment-mean costs TAU)/(mean bCBT -mean CBT-TAU). The mean costs, including all medical and non medical costs, of the patients in the blended eHealth condition will be subtracted from the mean costs of the patients in the TAU condition. This difference will be then be divided with the subtracted effects (case of response or remission on the BAI). This procedure will be bootstrapped 10,000 times, generating an estimation of the blended eHealth treatment groups’ incremental costs in relation to their incremental health benefit. Additionally an incremental cost-utility ratio (costs per QALY) will be calculated; this procedure is identical to the cost-effectiveness ratio with the exception that instead of a case of response or remission, an additional quality adjusted life year is calculated (QALY). Finally, to test the robustness of the results, we will conduct a sensitivity analyses, to investigate how sensitive the ICERs will be to changes of cost estimates (for example difference in costs per iCBT contact, type of psychologists and number of sessions). For decision-making purposes, the ICER acceptability curve will be plotted for various willingness-to-pay (WTP) ceilings, which helps making judgments about whether the blended intervention offers good value for money, relative to treatment as usual. One-way sensitivity analyses directed at uncertainty in the main cost drivers will be performed to gauge the robustness of our findings across a range of likely values of those parameters.

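### No planned analysis has a therapist level and the protocol does not say whether therapists serve one arm or both; if they are nested in arm, the cost-effectiveness intervals are too narrow

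*Protocol*

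**What the plan says.** Protocol section 10.1 (CEA/CUA) carries the main analysis. For costs, "p-values will be estimated using a multilevel model (with repeated measurements to control for dependency between the measurements", and the parameters are then bootstrapped. The incremental ratio is also bootstrapped, 10,000 times, and feeds the acceptability curve. No therapist or centre level is named for the model or for the resampling.

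Section 10.2 sets up the clinical mixed model "with participants as random effects, and time (T1-T3), group (blended vs. face-to-face treatment) and time x group as fixed effects". The baseline score is the only covariate, and the section calls these estimates descriptive.

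Section 4.4 states that "For this study a sample size of 156 is based on a formula to estimate the power of a cost-effectiveness analyses". The aim is to "provide an 80% chance (i.e., power) to be 95% confident that the therapy is good value". The formula has no design effect.

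Therapists deliver both treatments. In the blended arm, "The therapist monitors patients’ online progress and provides weekly feedback prior to the next face-to-face session". Section 8.2 randomises individual patients from a block table and mentions no stratification by centre or therapist. No section gives the number of therapists, their caseload, an ICC, or the assignment of therapists to arms.

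**The concern.** Patients of the same therapist tend to resemble one another in outcome and in resource use, and the protocol gives reasons to expect this. Section 5 leaves parallel treatment, including medication, to the practitioner's judgement. The number of sessions varies from 12 to 20, and section 8.1 collects therapist time and measures the alliance between patient and therapist.

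Shared therapists are very likely. Section 4.1 starts recruitment at one GGZ inGeest site, both Altrecht outpatient departments and Oss. That is four departments, so 156 / 4 = 39 trial patients each, or 156 / 6 = 26 if the two reserve locations open.

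What matters is how therapists relate to the arms. If each therapist works in one arm only, differences between therapists become part of the arm contrast, and an analysis with only a patient level leaves them out of the standard error. A difference between a few therapists could then pass for a treatment effect, in a trial meant to tell insurers and providers whether blended care is good value.

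**Working it through.** **1. The plan's own figure.** Inputs from section 4.4: z values 1.96 and 0.84, cost SD 800, effect SD 0.02, willingness to pay W = 80,000, cost difference C = 832, effect difference E = 0.02, correlation 0.1. The unsubscripted SDs in the printed formula are read as those of costs and effects, and the SD with subscript q as that of effects.

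- Variance of net benefit = 800² + (80,000 × 0.02)² − 2 × 80,000 × 0.1 × 800 × 0.02 = 640,000 + 2,560,000 − 256,000 = 2,944,000, so SD = 1,715.8.
- Difference = WE − C = 1,600 − 832 = 768.
- n per arm = 2 × (1.96 + 0.84)² × 2,944,000 / 768² = 78.26. The stated 78 per arm is reproduced.
- Power at 78 per arm = Φ(768 / (1,715.8 × √(2/78)) − 1.96) = Φ(2.795 − 1.96) = 79.8%.

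**2. Therapists nested in arm.** Let m be the number of trial patients per therapist. Both m and the ICC of net benefit are assumptions.

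- Design effect DE = 1 + (m − 1) × ICC.
- Width of the planned interval relative to the correct one = 1/√DE.
- Type I error when clustering is ignored = 2 × (1 − Φ(1.96/√DE)).
- Power when clustering is accounted for = Φ(2.795/√DE − 1.96).

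| m | ICC | DE | Relative width | Type I error | Power |
|---|---|---|---|---|---|
| 3 | 0.01 | 1.02 | 0.99 | 5.2% | 79.0% |
| 3 | 0.05 | 1.10 | 0.95 | 6.2% | 76.0% |
| 5 | 0.05 | 1.20 | 0.91 | 7.4% | 72.3% |
| 10 | 0.01 | 1.09 | 0.96 | 6.0% | 76.3% |
| 10 | 0.05 | 1.45 | 0.83 | 10.4% | 64.1% |
| 10 | 0.10 | 1.90 | 0.73 | 15.5% | 52.7% |

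With 78 patients per arm, m = 3 means 26 therapists per arm and m = 10 means about 8. These are normal approximations with equal caseloads. A simulation of 10,000 trials with 8 nested therapists per arm and ICC 0.05, analysed as independent patients, gave a type I error of 10.3%, in line with the table.

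**3. Therapists crossed with arm.** If each therapist treats both arms in balance and there is no therapist-by-arm effect, the variance of the contrast is multiplied by about (1 − ICC). A model with a therapist term then has power of 80.2%, 81.8% and 83.8% at ICC 0.01, 0.05 and 0.10. Ignoring therapists is slightly conservative: at ICC 0.05 the simulated type I error was 4.4%.

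**4. Sign of the cost difference.** The 78 per arm needs C = +832, which makes blended care dearer, but the text of section 4.4 expects it to cost less. With C = −832 the difference is 1,600 + 832 = 2,432 and n = 2 × 7.84 × 2,944,000 / 2,432² = 7.8 per arm. Power at 78 per arm then stays above 99.9% even with m = 10 and ICC 0.10. The power column therefore applies only to the calculation as written. The width and type I error columns do not use C.

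**The case against.** The strongest reply is that the harmful condition is not in the protocol. Nothing there describes therapist training or ties a therapist to an arm, both arms rest on the same treatment protocols, and patients are randomised individually. With many therapists and a small ICC the effect is negligible (first row of the table). Nor does the protocol justify an ICC of 0.05 for societal net benefit. Costs supply only 640,000 / 3,200,000 = 20% of its variance before the covariance term, and they include medication, other care and lost productivity as well as sessions. All of this stands, and it makes the point conditional.

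It can also be said that extra model levels and the resampling unit belong in a statistical analysis plan. This has some force for section 10.1, which names one dependency without excluding others. It has less for section 10.2, which lists its random and fixed effects and allows a single covariate. Either way, both sections describe their dependence structure and therapists are not in it.

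Three stronger readings are tempting, and the documents support none of them:

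- **That the 80% power is not delivered.** This needs nesting in arm, an ICC well above zero and C = +832. The first two are not documented, and the third conflicts with the wording of section 4.4.
- **That sharing three centres makes the intervals too narrow.** With individual randomisation, shared centres alone do not inflate the variance of the arm contrast.
- **That the fault in the clinical mixed model undermines the trial's conclusion.** That model is descriptive. The decision rests on the analysis in section 10.1.

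**Conclusion.** The point holds as a conditional weakness that is cheap to repair. As written, neither the cost model, the bootstrap, the clinical model nor the sample size formula has a therapist level, although therapists very probably each treat several trial patients. If they are nested in arm, the cost-effectiveness intervals and acceptability curve overstate certainty. Under the assumed caseloads and ICCs, type I error runs from about 5% to 15.5%, and the power calculated in section 4.4 runs from about 79% down to 53%, subject to the sign of C being reconciled. If therapists treat both arms in balance with no therapist-by-arm effect, the planned analysis is valid or slightly conservative. The protocol does not let the reader tell which case applies, so confidence in the size of the problem is low.

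**What to change.** - **Data and design:** record a code for each patient's treating therapist, and state the number of therapists and whether each delivers one treatment or both. Without the code, the dependence cannot be modelled afterwards.
- **Sections 10.1 and 10.2:** add a therapist random intercept and a fixed centre effect to the cost and clinical models.
- **Bootstrap:** let the resampling unit follow the actual assignment. If therapists are nested, resample by therapist within arm, without splitting into cells that hold too few therapists.
- **Section 4.4:** state that 80% power assumes no therapist clustering, show power over a range of caseload and ICC, and reconcile the sign of C with the text on expected costs.

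The sample size need not change. The cost is analysis wording and one data field that the centres' administrations should already hold. The downside is that intervals may widen and the stated power may look less favourable if therapists prove to be nested. If they are crossed, the therapist term costs nothing.

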## Interim analysis (if applicable)

# Not applicable ETHICAL CONSIDERATIONS

## Regulation statement

The study will be conducted according to the principles of the Declaration of Helsinki (seventh version, 2013) and in accordance with the Medical Research Involving Human Subjects Act (WMO).

## Recruitment and consent

Patients will be recruited within the Anxiety Disorder Department of the participating Mental Health Care site(s) of GGZ inGeest, GGZ Altrecht and GGZ Oost-Brabant in the Netherlands. All new patients indicate during their intake interview whether they are willing to participate in a study. All patients with a primary diagnosis of a severe anxiety disorder (panic disorder with or without agoraphobia, social phobia, and generalized anxiety disorder) who are willing to participate who have agreed to be approached are contacted by the researchers by telephone and asked to participate in the study. Participants then receive a letter containing information on the study and the informed consent form (including a return envelope).

After a week, the researchers will contact the patient again. When the patient is willing to participate, a trained researcher then screens the patients with respect to the inclusion and exclusion criteria based on the SCID-I diagnosis and the patient’s demographic characteristics, such-as age. TheSCID-I interview is performed over the telephone, unless the patient prefers to do this face-to-face at a GGZ inGeest, GGZ Altrecht or GGZ Oost-Brabant location.

Patients who are not eligible to participate will be notified and remitted to regular treatment trajectories within the participating specialized mental health care center(s). In case of acute threat of suicide the principal investigator will inform the professional responsible for treatment immediately via telephone and e-mail.

If patients are eligible to participate, written informed consent will be obtained via mail.

## Objection by minors or incapacitated subjects (if applicable)

## The blended CBT treatment that will be provided in this trial does not add risks to the CBT treatment as usual. The questionnaires can be considered a burden.

## Benefits and risks assessment, group relatedness

An insurance exemption is requested from the METC VUmc. No risks are associated with participation in the study.

## Compensation for injury

Not applicable.

The sponsor/investigator has a liability insurance which is in accordance with article 7, subsection 9 of the WMO.

The sponsor (also) has an insurance which is in accordance with the legal requirements in the Netherlands (Article 7 WMO and the Measure regarding Compulsory Insurance for Clinical Research in Humans of 23th June 2003). This insurance provides cover for damage to research subjects through injury or death caused by the study.

1. € 450.000,-- (i.e. four hundred and fifty thousand Euro) for death or injury for each subject who participates in the Research;
2. € 3.500.000,-- (i.e. three million five hundred thousand Euro) for death or injury for all subjects who participate in the Research;
3. € 5.000.000,-- (i.e. five million Euro) for the total damage incurred by the organisation for all damage disclosed by scientific research for the Sponsor as ‘verrichter’ in the meaning of said Act in each year of insurance coverage.

The insurance applies to the damage that becomes apparent during the study or within 4 years after the end of the study.

## Incentives (if applicable)

<*Please describe any special incentives, compensation or treatment that subjects will receive through participation in the study*.>

# ADMINISTRATIVE ASPECTS, MONITORING AND PUBLICATION

## Handling and storage of data and documents

During the study personal patient data (such as contact information, demographic variables and information concerning inclusion) will be stored in an administrative database at a GGZ inGeest server, which is secured with a password. The data will be collected as part of the regular intake procedure at GGZ inGeest, GGZ Altrecht and GGZ Oost-Brabant and is accessible to the partaking investigators ([name] and [name]). .

The data that are collected during the study (questionnaires at baseline, week 6-10, 12-20 and week 64-72), will be stored in secure databases on the secure servers of inGeest, GGZ Altrecht and GGZ Oost Brabant. The information that is needed for the current study will be transferred by a GGZ inGeest, GGZ Altrecht and GGZ Oost-Brabant data-manager to a secure database at the VU. The databases will be secured with a password that is only known to the principal investigators.

Participants will be registered with a seven-figure code with which they can be identified in the database. The first three numbers of the code refers to the center in which the participants receive treatment. The last three numbers refer to the patient. The link between the personal data and the number is kept in a password secured patient identification log-document that is only accessible to one investigator.

The data that is collected via the web-modules of the blended treatment will be stored at a MindDistrict server. MindDistrict operates according to the ISO 27001 norm (International Organization for Standardization, 2005) and is currently in the process of becoming certified according to the ISO 27001 norm. The hosting party is ISO 27001 certified. Information that will be collected via the online questionnaires is collected with NetQuestionnaire. The information acquired via NetQuestionnaire is stored at servers at GGZ inGeest.
All online data will be sent via HTTPS with a SSL-certificate (AES-256 and SHA-1, RSA (2048 bits)). HTTPS entails an extension to the HTTP-protocol (the protocol for communication between a webclient and a webserver) with which the information is encrypted during transfer, so an outsider or intruder should not be possible to access the information.

## Monitoring and Quality Assurance

The study will be conducted according to the recommendations of the quality handbook of EMGO+ (<http://www.emgo.nl/kc/>). The investigators have received training in following the rules and regulations that are stated in the handbook. The quality of data collection is further strengthened by the support of the data-management staff of GGZ inGeest. The quality of the study procedures are not otherwise monitored, but there is a possibility that the study will be randomly selected for an independent audit of EMGO+.

## Amendments

Amendments are changes made to the research after a favorable opinion by the accredited METC has been given. All amendments will be notified to the METC that gave a favorable opinion.

Non-substantial amendments will not be notified to the accredited METC and the competent authority, but will be recorded and filed by the sponsor.

<*The following text is applicable for studies with an investigational medicinal product.*>

A ‘substantial amendment’ is defined as an amendment to the terms of the METC application, or to the protocol or any other supporting documentation, that is likely to affect to a significant degree:

- the safety or physical or mental integrity of the subjects of the trial;
- the scientific value of the trial;
- the conduct or management of the trial; or
- the quality or safety of any intervention used in the trial.

All substantial amendments will be notified to the METC and to the competent authority.

Non-substantial amendments will not be notified to the accredited METC and the competent authority, but will be recorded and filed by the sponsor.

< *Examples of non-substantial amendments are typing errors and administrative changes like changes in names, telephone numbers and other contact details of involved persons mentioned in the submitted study documentation*.>

